### Analysis

This study is designed to evaluate the beneficial effect of learning therapy in elderly people. We calculate the change score (post-training score minus pre-training score) in all cognitive function measures. We conduct an ANCOVA for the change scores in each cognitive test. The change scores are the dependent variable. Groups (learning therapy, waiting list) are the independent variable. Pre-training scores in the dependent variable, sex, age categories are the covariates to exclude the possibility that any pre-existing difference of measure between groups affect the result of each measure and to adjust for background characteristics. The level of significance is set at p < 0.05. Moreover, we report eta squared (*η^2^*) as an index of effect size. It is the standardized difference in the change score between intervention groups (learning therapy group, waiting list group). In actuality, *η^2 ^*≥ 0.01 is regarded as a small effect, *η*^2 ^≥ .006 as a medium effect, and *η^2 ^*≥ 0.14 as a large effect [80]. Missing data are imputed using the expectation-maximization method, as implemented in the Statistical Package for the Social Sciences (SPSS) Missing Value Analysis. It imputes missing values using maximum likelihood estimation with the observed data in an iterative process [81]. All randomized participants are included in the analyses in line with their allocation, irrespective of how many sessions they complete (intention-to-treat principle). All analyses are performed using SPSS software (ver. 18 or higher).

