### Sample size

Our sample size estimation is based on the change score in the reverse ST, which is the primary outcome in this study. We expected to detect a large effect size (*η*^2 ^= 0.14) of the change score in the reverse ST between learning therapy and waiting list groups. the sample size was determined using G * power [78,79] based on 80% power, a two-sided hypothesis test, an alpha level of 5%, an analysis of covariance (ANCOVA) model that includes a baseline reverse Stroop task score, age, and sex as a covariate. The sample size calculation indicated that we need 32 participants in each of the learning therapy and waiting list groups with consideration of a 20% drop-out rate.

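### Filling missing post-tests once by EM and analysing them as observed gives either a 5% test that runs at about 12% or an effect 20-25% too small, if the full 20% drop-out allowance is lost

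*Protocol article*

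**What the plan says.** The Analysis section of the protocol article sets one rule for missing data: "Missing data are imputed using the expectation-maximization method, as implemented in the Statistical Package for the Social Sciences (SPSS) Missing Value Analysis". It describes the rule this way: "It imputes missing values using maximum likelihood estimation with the observed data in an iterative process". Multiple imputation, an added residual and a variance correction are not mentioned.

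The completed data then go into an ANCOVA of change scores on group, with pre-training score, sex and age category as covariates. The analysis set is everyone randomised: "All randomized participants are included in the analyses in line with their allocation, irrespective of how many sessions they complete (intention-to-treat principle"). On the test, the section says: "The level of significance is set at p < 0.05".

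The Sample size section gives "32 participants in each of the learning therapy and waiting list groups with consideration of a 20% drop-out rate". The overview of cognitive measures has one assessment before the intervention period and one after it, so a dropout who misses the second visit has no post-baseline score at all.

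**The concern.** An EM fill is a predicted value from a model fitted to the people who were observed. For a dropout with no post-baseline data it adds no information about the group difference. The ANCOVA cannot tell a prediction from a measurement, so it counts the filled score in the sample size and in the error degrees of freedom.

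The trial was sized on about 51 completers, but the analysis would claim the precision of 64. The rule applies to the primary Stroop outcome and to every secondary outcome. Depending on what is in the EM model, it gives either too many false positives or a diluted effect estimate, and eta squared is diluted with it.

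**Working it through.** **Inputs from the article.** 64 randomised (32 + 32); 20% drop-out allowance; two-sided 5% test; 80% power; eta squared 0.14; ANCOVA with baseline score, age and sex (5 fitted parameters including intercept and group).

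**Assumptions, not in the article.** All of the allowance becomes missing post-tests. Post-tests are missing at random (completely at random in the simulations). The pre-post correlation is 0.7, or 0.6 in a second run. Filled values are predicted values with no residual added.

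**Step 1: the plan's own figure.** f² = 0.14/0.86 = 0.163. With noncentrality f² × N and error df N − 5, N = 51 gives 80.5% power. Then 51/0.80 = 63.75, so 64 = 2 × 32. The stated sample size reproduces and is not in question.

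**Step 2: closed form, group in the EM model.** The 13 filled scores lie on the fitted surface. They leave the residual sum of squares of the 51 completers unchanged, but raise the error df from 46 to 59 and the apparent sample size from 51 to 64.

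- Reported SE / true SE ≈ √[(46/59) × (51/64)] = √(0.780 × 0.797) = 0.788.
- The nominal critical value on 59 df is 2.001. The effective one is 2.001 × 0.788 = 1.577.
- Actual type I error = 2 × P(t on 46 df > 1.577) = 12.2%, so coverage is about 87.8%.
- With 6 missing: √[(53/59) × (58/64)] = 0.902; 2 × P(t on 53 df > 1.805) = 7.7%.

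**Step 3: simulation.** With eta squared 0.14, d = 2 × √0.163 = 0.807 residual SDs. In post-test SDs that is 0.807 × √(1 − 0.7²) = 0.576 at correlation 0.7, and 0.807 × 0.8 = 0.646 at correlation 0.6.

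Correlation 0.7, 13 missing (split 6/7 or 11/2), 6,000 trials per case:

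| Analysis | Type I error | Estimate at planned effect 0.576 | 95% CI coverage |
|---|---|---|---|
| EM fill, group in model | 12.5-12.7% (SE 0.161 reported, 0.206-0.208 true) | – | about 87-88% |
| EM fill, group not in model | 4.7% | 0.44-0.45 (22-24% too small) | 87.5% at the planned effect |
| Observed post-tests only | 4.6-4.9% | unbiased | 95% |

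Correlation 0.6, 12 missing, 20,000 trials under the null and 10,000 at the planned effect:

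| Analysis | Type I error | Mean reported SE / true SE | Estimate at planned effect 0.646 | Rejection at planned effect |
|---|---|---|---|---|
| EM fill, group in model | 11.3% | 0.182 / 0.228 | 0.643 | 88% |
| EM fill, by arm | 11.7% | 0.184 / 0.232 | – | – |
| EM fill, group not in model | 4.9% | 0.183 / 0.185 | 0.518 (20% too small) | 79% |
| Observed post-tests only | 5.05% | 0.228 / 0.229 | 0.645 | 78% |

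With group in the model, 5 to 10 auxiliary baseline variables leave type I error at 11.5-12.0%. Drop-out of 30% in one arm and 10% in the other gives 12.5%, and 6 missing gives 8.0%.

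Without group in the model, dropouts in both arms are filled from one pooled regression. That pulls the arms together by roughly the missing share (13/64 = 20%). The reported SE then matches the shrunken estimator's own variation, which is why the test keeps its level under the null while the estimate is biased.

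**The case against.** A reader might infer that the planned test simply runs at 12%. The article does not support that without a condition. It does not say whether group is in the EM model, and if it is left out the test holds about 5% and rejects at the planned effect about as often as the observed-case analysis (79% against 78%). In that case the p-value is hardly affected, and the bias goes against the therapy. This stands: the 12% belongs to one of two readings.

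A reader might also take 20% missing post-tests as what the sponsor expects. The Sample size section gives it as an allowance. Someone who stops training may still attend the post-test, since the analysis keeps participants whatever number of sessions they complete. This stands too, and it is why the figure for 6 missing is given beside the one for 13.

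Third, the list of variables in an imputation model is the kind of detail that an article leaves to a fuller document. I agree, and its absence is not part of this point. It is only the condition on which the size depends. What the article does fix is a single fill followed by an ordinary ANCOVA on everyone randomised, and neither reading of that rule gives sound estimates and intervals when there is an effect to estimate.

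**Conclusion.** The point holds in conditional form. The stated rule treats filled scores as data. If the full allowance is lost (13 of 64), data are missing at random and the pre-post correlation is about 0.7:

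- **Group in the EM model, or EM by arm:** SE about 0.79 of its true value, type I error about 12%, coverage about 87-88%. With 6 missing, type I error is about 8%.
- **Group not in the EM model:** type I error about 5%, effect about 20-25% too small, eta squared also pulled toward zero, and coverage about 88% at the planned effect. Coverage under the null is not harmed.

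The supported range for type I error at the full allowance is therefore about 5% to 12%, and the low end comes with a biased estimate. The direction does not depend on the assumed correlation: 0.6 and 0.7 give the same picture. The sample size is not affected.

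**What to change.** Replace the EM fill-in. For the primary analysis, fit the ANCOVA to observed post-tests (or change scores), with participants in their allocated group and adjustment for pre-training score, age and sex. With a single post-test this is valid under missing at random given those covariates. It holds type I error at about 5% and coverage at about 95%. By the plan's own inputs it has 80.5% power at 51 observed (78% in the simulation at 52 observed), which is how the trial was sized.

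If all 64 are to stay in the model, use multiple imputation with group, pre-training scores, age and sex in the imputation model, and combine the results by Rubin's rules. Multiple imputation was not simulated here, but a valid version should also hold about 5%.

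If departures from missing at random are examined, use reference-based multiple imputation. Setting learning-therapy dropouts to the waiting-list mean would be another single deterministic fill and would repeat the fault.

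The cost is a change of analysis wording, and wider intervals than the EM fill-in would report.

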## Discussion

This study is designed to investigate the beneficial effects of learning therapy on widely various cognitive functions such as executive functions, episodic memory, short-term memory, working memory, reading ability, attention, and processing speed in healthy elderly people.

This study has several strengths compared to earlier studies using cognitive training for elderly people. First, this study was designed according to CONSORT guidelines [66]http://www.consort-statement.org/consort-statement/, which are intended to improve standards of reporting of randomized clinical trials (RCT). Consequently, this study has been structured to enable its reproduction in both research and clinical settings. Moreover, we can provide sufficient evidence of the effectiveness of cognitive training such as learning therapy.

Second, we investigate the beneficial effects of learning therapy on widely various cognitive functions. The measures assess cognitive functions of seven categories: executive functions, episodic memory, short-term memory, working memory, reading ability, attention, and processing speed. Various cognitive functions are necessary to support our actions and behaviours in everyday life. For instance, when we cook meals, we must: (1) choose a menu (executive functions); (2) remember the refrigerator contents (memory); (3) seek and select seasonings from storage (attention); and (4) cut and prepare cooking ingredients with speed and efficiency (processing speed). Because of the complexity of such an apparently simple task, it is expected to be important to investigate the beneficial effects of learning therapy on widely various cognitive functions.

Third, we use simple, easily learned training tasks (reading aloud and simple calculation) using paper and pencil. Most training tasks in previous studies were complex tasks using computers [18,31,82-84]. Using computers might make it easy to record data precisely and to control tasks. Nevertheless, elderly people often have difficulty using computers [85-87]. The difficulty using computers might cause frustration and other negative emotion, possibly reducing their motivation to continue. Our training tasks are more familiar to elderly people and thus expected to encourage their willingness.

This study has some limitations. A first limitation is the intervention period. Our intervention period is about 6 months. Some previous studies have shown that short-term intervention (four example 4 to 6 weeks) improved cognitive function in elderly people [18,20]. Considering reduced costs for elderly people, shorter intervention studies using learning therapy would be also needed. A second limitation is participants. We recruit only healthy elderly people for participation in this study. Providing the validity of effects of learning therapy on widely various cognitive functions, we must conduct the same randomized controlled trial (RCT) for non-healthy elderly people such as those with dementia or depression.

In summary, this study is the first to reveal the beneficial effects of learning therapy on a wide range of cognitive functions in elderly people. Our study is designed to provide sufficient evidence of effectiveness of learning therapy. Given that most cognitive functions decrease with age [1] and that these functions are strongly correlated with daily life activities [7-9], our results can elucidate the effects of cognitive training for elderly people.

## Trial status

Recruitment of participants begins in February 2012, and is expected to end in January 2013.

## Abbreviations

ANCOVA: Analysis of covariance; Cd: Digit symbol coding; CONSORT: Consolidated standards of reporting trials; D-CAT: Digit cancellation task; DS-B: Digit span backward; DS-F: Digit span forward; FS-N: First and second names; IQ: Intelligence quotient; JART: Japanese reading test; LM: Logical memory; MRI: Magnetic resonance imaging; RCT: Randomized controlled trial; RBMT: Rivermead behavioral memory test; SPSS: Statistical package for the social sciences; SS: Symbol search; ST: Stroop test; UMIN: University Hospital Medical Information Network; VBM: Voxel based morphometry; VFT: Verbal fluency task; WAIS-III: Wechsler Adult Intelligence Scale-Third Edition; WMS-R: Wechsler memory scale-revised.
